## **Secondary target figure**

The secondary target figure is aimed towards the support of wound healing by the applied amniotic membrane clamped into AmnioClip. Provided that the amniotic membrane holder is well tolerated, it will be assessed whether an improvement has occurred or not at the end of the observation period.

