The proposed project is acceptable from an ethical point of view, since it is already known that large contact lenses or scleral shells are compatible on the eye surface. The insetion of the amniotic membrane holder AmnioClip into the palpebral fissure can be controlled by means of a slit-lamp examination. The removal of the amniotic holder AmnioClip is possible at any time without problems. This is where the clinical relevance of the pilot study comes to the fore. A ring covered with an amnion which is placed as a contact lens on the eye may be inserted or removed at any time without any surgical effort.

Together with the spanned amniotic membrane, the amniotic membrane holder can be distributed by eye banks or companies to hospitals or surgeries.

The observation of a placebo group is not necessary, because suturing of an amniotic membrane has been enforced through many trials and observations against an ointment therapy.

Aim of the project:

The primary objective of this project is to examine the mounting and compatibility of the amniotic membrane holder including the amniotic membrane (AmnioClip) in the eye of the patient.

The secondary objective of the study is to examine to what extent the underlying disease can be improved during the observation period (1 week). This is done without a control group.

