**6. Procedure of the clinical trial see III****III. Questions to patients and probands**

10 persons are involved in the pilot study.

It is planned to involve the patients starting Feb 2011.

The postoperative observation period amounts one week. Dependent upon compatibility, the postoperative observation period may be extended to 4 weeks.

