### **Assessment of the effectiveness**

The assessment of effectiveness is performed by daily visit of the probands and by assessment of the anterior eye segment. The primary key performance target of the trial refers to the compatibility of the developed amniotic membrane holder.

If the following points are applicable for one week:

- complete eyelid closure is possible,
- ring does not touch the cornea,
- amniotic membrane is clamped firmly in the holder and is located on the cornea,
- no pain or discomfort occurs,

then this will be considered as a success.

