## **VI. Interim analysis and criteria for discontinuation**

The therapeutic trial will be finished prematurely, if:

- two of the first five patients do not tolerate the amniotic holder,
- the rate of patient recruitment is inadequate,
- serious, unresolvable problems concerning the quality of the captured data occur,
- unforeseen circumstances occur which do not allow a continuation of the therapeutic trial,
- unacceptable risks and toxicities occur (decision in accordance with a performed new benefit-risk assessment),
- new scientific results during the term of the therapeutic trial do not permit to continue with this therapeutic trial.

The LKP decides on the discontinuation of the clinical trial.

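### The healing endpoint is assessed only if the holder is well tolerated, a condition set after treatment that conflicts with the unconditional one-week objective and probably flatters the result

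*Protocol*

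**What the plan says.** The aim in section II.1 of the Protocol (Brief summary of the project) reads: "The secondary objective of the study is to examine to what extent the underlying disease can be improved during the observation period (1 week"). It names no condition, and it adds: "This is done without a control group". Section III gives the size: "10 persons are involved in the pilot study".

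The endpoint meant to serve this objective, under Secondary target figure, does carry a condition: "Provided that the amniotic membrane holder is well tolerated, it will be assessed whether an improvement has occurred or not". The judgement is made when observation ends, and section III makes that time variable: "Dependent upon compatibility, the postoperative observation period may be extended to 4 weeks".

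The primary endpoint, under Assessment of the effectiveness, is compatibility over one week. One of its four criteria is that "no pain or discomfort occurs". The protocol also foresees patients who do badly with the device. Section II.1 notes that "The removal of the amniotic holder AmnioClip is possible at any time without problems", and section VI lists as a reason to stop that "two of the first five patients do not tolerate the amniotic holder".

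**The concern.** Tolerance is an outcome of the treatment. An endpoint restricted to patients with a good outcome describes a group that could not be identified when the holder was placed. The objective asks what happens to the disease in the treated patients, while the endpoint as worded answers for those in whom the device worked.

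There is no control group, so the healing result will be read as a plain proportion and the choice of denominator goes straight into it. With ten patients, leaving out two or three changes the message. The protocol does not tie the term well tolerated to the four success criteria or to the stopping rule, and the study is open. Whether a patient counts could therefore be settled with the healing result in view.

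**Working it through.** The protocol states no expected improvement rate and no expected tolerance rate, so it has no figure to reproduce. All rates below are assumptions. Only the sample size of 10 (section III) and the stopping limit (section VI) come from the document.

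**Size of the distortion if the proviso applies per patient.** Let f be the share of patients not tolerating, p the improvement rate in tolerators and q the rate in non-tolerators.

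- Rate in tolerators only: p
- Rate in all treated: (1 − f) × p + f × q
- Difference: p − [(1 − f) × p + f × q] = f × (p − q)

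For p = 0.80 and 2 of 10 intolerant (f = 0.2):

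- q = 0: all treated 0.8 × 0.80 + 0.2 × 0 = 0.64, difference +0.16
- q = 0.40: all treated 0.64 + 0.2 × 0.40 = 0.72, difference +0.08
- q = 0.80: all treated 0.64 + 0.2 × 0.80 = 0.80, difference 0

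Across the number intolerant, in percentage points with p = 0.80:

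| Intolerant of 10 | q = 0 | q = 0.40 | q = 0.80 |
|---|---|---|---|
| 1 | +8 | +4 | 0 |
| 2 | +16 | +8 | 0 |
| 3 | +24 | +12 | 0 |

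The sign can reverse. With p = 0.60, q = 0.80 and f = 0.2, the difference is 0.2 × (0.60 − 0.80) = −0.04, or −4 points.

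**The same in whole patients.** Suppose 8 of 10 tolerate the holder and 6 of those 8 improve. The tolerator-only figure is 6/8 = 75.0% (exact 95% interval 34.9 to 96.8). If neither of the other two improves, the all-treated figure is 6/10 = 60.0% (26.2 to 87.8). If both improve, it is 8/10 = 80%.

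**Whether such patients are likely to exist.** If the true intolerance probability is 10%, 20% or 30%, and early stopping is ignored, the chance of at least one non-tolerator among 10 is:

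- 1 − 0.9^10 = 65%
- 1 − 0.8^10 = 89%
- 1 − 0.7^10 = 97%

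The numerical stopping limit looks only at the first five patients. One intolerant patient among those and any number among the last five would not meet it, so up to 1 + 5 = 6 of 10 could fall outside the secondary endpoint without that limit being reached.

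**Direction.** Section II.1 holds that the membrane is rich in growth factors and strongly supports healing. On that premise a patient who loses the membrane early should improve less often, so q < p and the difference is positive. This is an inference from the protocol's reasoning. The document gives no figure for it.

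**If the proviso applies to the study as a whole.** No individual patient is dropped, so the formula does not apply. Healing is then assessed only when the device has done well overall, and a poorly tolerated series would yield no healing result at all. The objective in section II.1 makes no such exception.

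**The case against.** The case on the other side has five parts.

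- **The wording concerns the holder, not each patient.** It may describe a sequence: establish compatibility first, then look at healing. This reading is tenable and fits the stopping rule. It does not rescue the text, because reporting healing only after a favourable primary result depends on the outcome and also departs from the stated objective.
- **The sentence defines no rate or denominator, and analysis sets may be left to a statistical analysis plan.** This is correct, and the absence of an analysis set is not held against the protocol. The objection is to the proviso, which the protocol does state.
- **The data are collected anyway.** A reader might infer that no outcome record would exist for patients who do not tolerate the holder. The documents do not support that. Visits 3 and 4 provide inspection of the eye and photographs, Visit 5 has a final eye examination with no tolerance condition, and effectiveness is said to be followed by daily visits. What is at risk is these patients' place in the endpoint.
- **Upward bias is not certain.** A reader might also infer that the rate must be inflated by one divided by the share tolerating. That holds only if no non-tolerator improves. A patient with discomfort might still wear the holder to day 7 and heal. The bias can be smaller, zero or negative.
- **The endpoint is secondary, in an uncontrolled pilot of 10.** The primary endpoint is untouched and would itself show the intolerant patients. This limits the severity.

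**Conclusion.** The point holds at moderate severity. The endpoint wording makes the healing assessment depend on a post-treatment outcome that overlaps with the primary endpoint, and it contradicts the unconditional one-week objective. Both readings of the proviso lead to a selected healing result.

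On the per-patient reading the bias is f × (p − q): +16, +8 or 0 points for 2 of 10 intolerant and p = 0.80, according to whether q is 0, 0.40 or equal to p. An upward direction is probable and rests on the protocol's premise that membrane contact promotes healing. The sizes rest entirely on assumed rates. With intervals as wide as those shown, the harm is a misleading description rather than a wrong formal conclusion.

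**What to change.** Delete the proviso from Secondary target figure. State that improvement is evaluated at week 1 in every patient in whom a holder was placed, whatever the tolerance, so that the endpoint matches the one-week objective in section II.1. Report improved over all treated as the main figure, and count early removal without documented improvement as not improved. Show the rate among tolerators as supportive, and likewise any later assessment in patients who wear the holder longer.

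The change affects counting only and leaves treatment as it is. It uses the Visit 5 examination that is already scheduled. Two clarifications go with it, because the visit text does not address these cases: the week-1 evaluation also applies after early removal, and it also applies to patients whose final visit is moved to a later date. The cost is a few sentences and a stated rate that may be less favourable.

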**Inclusion criteria**

- male and female patients between 18 and 85 years
- epithelial defects of the cornea of different genesis (eg after injury, after acid burns, in autoimmune diseases such as rheumatoid arthritis)
- incipient corneal ulcer, unless there is no bacterial infection
- existence of the declaration of patient consent

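### The secondary objective asks how far the eye improves within one week, but the endpoint is an undefined yes/no call at a variable time, which answers that only coarsely

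*Protocol*

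**What the plan says.** The aims in section II.1 of the protocol (Brief summary of the project) set the secondary objective as examining "to what extent the underlying disease can be improved during the observation period (1 week"), and add: "This is done without a control group".

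The matching endpoint is in section III under Secondary target figure. It speaks of the membrane's support for wound healing and defines the result in one clause: "it will be assessed whether an improvement has occurred or not at the end of the observation period". No size, grade or threshold is attached. The judgement is made only for a holder that the eye accepts without trouble.

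Three further statements in section III bear on this:
- The number of patients: "10 persons are involved in the pilot study".
- The case mix: the inclusion criteria admit "epithelial defects of the cornea of different genesis", with injury, acid burns and autoimmune disease as examples, and incipient corneal ulcer as well.
- The duration: one week after placement, but "Dependent upon compatibility, the postoperative observation period may be extended to 4 weeks". The entry for following visits covers days 8 to 30.

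The design table in section II.5 marks the project as open.

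**The concern.** An objective about extent needs a variable that carries extent. Here the protocol fixes the variable as binary, so the size of any healing is lost when the endpoint is recorded. Because the call is made openly and without a stated criterion, it also depends on who makes it.

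The time differs too. The objective is tied to one week, the endpoint to the end of an observation period that varies between patients. A yes at day 7 and a yes at about 4 weeks are different findings, and a simple count would merge them.

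What is at stake is the healing information from the pilot. With ten patients and no comparison group, individual measurements are most of what it can offer on healing. A single count across fresh injuries, burns, autoimmune defects and early ulcers is hard to interpret.

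**Working it through.** The protocol gives no figure for this endpoint, so there is nothing to reproduce. The check compares the texts and then uses a small illustration with assumed data.

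**Objective against endpoint**

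| | Objective (section II.1) | Endpoint (section III, Secondary target figure) |
|---|---|---|
| Quantity | extent of improvement | improved or not |
| Time | 1 week | end of observation: day 7, or later (to about 4 weeks) with extended wear |
| Criterion | none given | none given |

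**What the visits collect**
- Visit 1 (baseline): an ophthalmological examination, content not specified.
- Visits 3 and 4 (days 1 and 3): holder position, inspection, questions on pain and well-being, photographs.
- Visit 5 (day 7): holder removed, final ophthalmological examination, content not specified.
- Extended wear: a later final visit with a slit-lamp examination.

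The section on effectiveness adds assessment of the anterior segment, again without a scale. No visit names defect size, percentage closure or any other graded healing measure. Photographs are listed only for days 1 and 3, while the holder is in place, so the plan does not secure grading of baseline against final state from photographs.

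**Illustration (defect areas are assumed)**

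Percentage reduction = (baseline area − final area) / baseline area.
- 20 to 19 mm²: (20 − 19)/20 = 5%.
- 20 to 0 mm²: (20 − 0)/20 = 100%.

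Scenario A: all 10 defects shrink by 5%. Scenario B: all 10 close.

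| | A | B |
|---|---|---|
| Improved, if the assessor counts any shrinkage | 10/10 | 10/10 |
| Improved, if the assessor requires closure | 0/10 | 10/10 |
| Mean reduction in area | 5% | 100% |
| Complete closure | 0/10 | 10/10 |

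The wording permits either assessor's rule. Under the first, A and B cannot be told apart. Under the second, partial healing disappears. The two measured rows separate the scenarios whoever assesses.

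**Precision of the count**

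When all n patients are called improved, the exact (Clopper-Pearson) 95% lower limit is 0.025^(1/n). For n = 10 this is 0.025^0.1 = 0.692, so 10/10 has an interval of 69.2% to 100%. If the tolerance condition left 8 or 6 patients assessed (assumed numbers), the lower limits would be 63.1% and 54.1%. These limits describe the share called improved and say nothing about how much improvement occurred.

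**The case against.** The strongest reply is that the objective does not say the extent is meant per patient. Read for the group, the share of ten patients who improved is an answer to the question. This stands. A reader might infer that the objective cannot be answered at all, but the documents do not support that: the endpoint answers it coarsely.

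A reader might also infer that any shrinkage, however slight, must count as improvement. The protocol states no such rule. The criterion is open, and an assessor could decline to count a 5% change. What remains is that the result depends on the assessor and that partial and complete healing can be scored alike.

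The definition of improvement could sit in an SAP that is not at hand, so its absence alone is not the point. But the protocol itself fixes the yes/no form. A threshold added later would still give a binary result, and no later document can supply baseline sizes that were never recorded. An ophthalmological examination may include them in practice, but the protocol does not commit to it.

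Two further inferences should not be drawn:
- That the objective concerns a systemic disease such as rheumatoid arthritis. In context it is the ocular surface condition: the summary opens with surface defects, and patients enter on the corneal defect. This is loose wording only.
- That open assessment has pushed the call towards improvement. It makes bias possible, but nothing in the documents shows its direction or size.

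Nor does the protocol say that the pilot must supply a healing figure for a later controlled trial, so no failure on that ground can be charged to it.

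**Conclusion.** The point holds as a mismatch between objective and endpoint. The objective asks for extent within one week. The endpoint yields an assessor-dependent yes/no at day 7 or at a later time of up to about 4 weeks. The plan therefore answers its secondary question only as a share improved, across mixed causes and without a control group.

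In the assumed example, the same 5% shrinkage in all ten patients could be reported as 0/10 or 10/10, and the latter matches the result for ten complete closures. The defect sizes are invented to show the mechanism. The mismatch itself rests on the protocol's wording alone.

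Importance is minor to moderate. The aim is secondary and descriptive, and the primary conclusion on compatibility, which has its own four listed criteria, is unaffected.

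**What to change.** Under Secondary target figure, replace the yes/no call with a measured epithelial defect size, for example two perpendicular diameters. Record it at the baseline and day 7 ophthalmological examinations. If wear is extended, record it at that final visit too, and report that result separately so that time points are not mixed.

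Report for each patient:
- the percentage change in area, 100 × (baseline product of diameters − later product) / baseline product;
- complete closure, yes or no;
- the cause of the defect, with the listing ordered by cause.

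Describe incipient ulcers separately, because area alone does not capture them. State how many patients were not assessed for healing because the holder was not tolerated, so that the denominator is visible. Align the objective in section II.1 and the endpoint in section III on the ocular surface defect and on the same time point.

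The cost is a few minutes of measuring and recording at visits that already exist, plus a wording change. No patients, visits or control arm are added. Diameters are one workable choice among several. The protocol names a slit lamp only for checking insertion and for the extended-wear visit, so the method of measurement should be stated for baseline and day 7. The result may look less favourable than a count of improved patients. Baseline size has to be recorded before the holder is placed, since it may not be recoverable later.

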## **IV. Questions about the requirements of the planned research project**

### **1. Previous knowledge and experiences from the formulation of the question**

Concerning to this, please see above under 'Introduction' (state of knowledge)

a) from preclinical trials (animal experiments, § 40 paragraph 1 section 5 AMG)

omitted

Planned test dose in humans:

Omitted

Description of the amniotic membrane holder (AmnioClip) see attachment

**Specialized information or investigator brochure (for non-approved drugs) is enclosed.**

### Risk-benefit assessment

Due to a good compatibility, the amniotic membrane does not provides any significant side effects, and the membrane is approved for medical use. Any potential side effect can only be of mechanical nature, such as the development of dents or pressure marks in the area of the con-junctiva. The investigation of these undesirable effects is - among other things - subject of this study.

The standard procedure is to suture the amniotic membranes onto the ocular surface, so that a definite and good standard is specified in this connection. The here described new method is merely a new form of application of an amniotic membrane.

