## II. Research project

### 1. Brief summary of the project

Surface defects of the eye are difficult to treat and occur after injuries such as acid burns, or are caused by autoimmune diseases such as rheumatoid arthritis, in which the cornea with ulceration is involved particularly at higher age. Even after penetrating keratoplasty, disturbances of the epithelization can occasionally occur. The use of commercially available eye drops to foster wound healing is generally not very effective, because they cannot support proliferation of the corneal epithelium. The treatment is usually tedious. Clinical trials with growth factor containing eye drops were carried out many years ago, but did not provide any results. Todate, locally applicable drugs based on the basis of a growth factor are not available. Thus, disturbances in wound healing require consuming and tedious ointment and drop therapies. This also involves long stays at hospi-tals for these patients. During the treatment, cloudiness often occurs in the area of the corneal stroma. Thus a visual worsening or even blindness in the affected eye may be a consequence.

In the clinical practice, surgical application of an amniotic membrane by suturing onto the ocular surface has been proven as a very good alternative. The amniotic membrane is obtained after cesarean birth (cesarean section) and can be stored for a certain time in special media or freeze-dried. Meanwhile, there are many trials on the effectiveness of this method (see accompanying review article). The amniotic membrane is sutured onto the ocular surface of the patient, i.e. the membrane is fixed with a continuous thread or with individual sutures. Amniotic membrane is considered to be poorly immunogenic and it is obviously rich in growth factors, so that the healing process strongly is promoted under normal circumstances. The clinical results are significantly better in comparison to a

conventional ointment or drop therapy or in comparison to the application of contact lenses.

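### The compatibility rule contains no objective finding on the eye, so an eye with pressure marks, inflammation, infection or corneal worsening but no pain or discomfort is scored a success

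*Protocol*

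**What the plan says.** The aim of the project (Protocol, II.1) makes the mounting and compatibility of the holder, with the membrane in it, the primary objective.

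*Assessment of the effectiveness* turns this into a rule with four points, all to hold for one week: the lids can close fully, the ring stays clear of the cornea, the membrane is held fast and lies over the cornea, and "no pain or discomfort occurs". *Secondary target figure* asks whether the underlying condition improved or not, and only where the holder is well tolerated.

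The risk-benefit assessment states "the amniotic membrane does not provides any significant side effects, and the membrane is approved for medical use" and continues "Any potential side effect can only be of mechanical nature", with conjunctival dents and pressure marks as its examples. It adds: "The investigation of these undesirable effects is - among other things - subject of this study". Section VI lists, among the reasons for ending the trial early, "unacceptable risks and toxicities occur (decision in accordance with a performed new benefit-risk assessment").

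The eye is examined at baseline (Visit 1), inspected and photographed on days 1 and 3, and examined again on day 7. If wear is extended, there is a slit-lamp examination at a later final visit.

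**The concern.** In a pilot study of compatibility, the main result is the number of eyes that meet the success rule. Three of its points describe fit and position, and the fourth is a symptom. What the examiner sees on the conjunctiva and cornea does not enter. The study could therefore report an eye as compatible although an examination required by the protocol showed a lesion caused by the device or a reaction to it. The enrolled eyes already have epithelial defects or an incipient ulcer, so corneal worsening is a relevant outcome. The side effects that the protocol itself names do not count against success either.

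**Working it through.** **Inputs.** Sample size 10 (section III). The four success points (*Assessment of the effectiveness*). The secondary outcome (*Secondary target figure*). The named side effects (risk-benefit assessment). The protocol gives no success threshold, no expected event rate and no derivation of the 10 patients, so there is no planned figure to reproduce.

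**1. What each point observes.**

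| Point | What it observes | Can an objective ocular sign alone make it fail? |
|---|---|---|
| Lid closure | Fit | No |
| Ring clear of cornea | Position | No |
| Membrane secure and in place | Fixation | No |
| No pain or discomfort | Symptom | No, only through a symptom |

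**2. Logic.** Let A, B, C and D be 1 when the respective point is met. Success = A × B × C × D. Let S = 1 if the examiner finds new pressure marks, inflammation, infection or corneal worsening. S does not appear in the product.

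- S = 1 with pain or discomfort: D = 0, so the eye fails.
- S = 1 without either symptom, and A = B = C = 1: the product is 1, so the eye is a success.

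The gap is exactly the second case.

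**3. Secondary outcome.** It has two levels, so a worsened eye and an unchanged eye are recorded alike. It is assessed only if the holder is well tolerated, so an eye that does not tolerate the holder has no healing outcome at all. It cannot stand in for the missing item.

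**4. Size.** One reclassified eye changes the proportion by 1/10 = 10 percentage points. Exact (Clopper-Pearson) 95% limits:

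- 9/10: the lower limit solves 10p⁹(1 − p) + p¹⁰ = 0.025, giving 55.5%. The upper limit is 0.975^(1/10) = 99.7%.
- 10/10: the lower limit is 0.025^(1/10) = 69.2%. The upper limit is 100%.

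**5. How likely is at least one such eye?** The protocol gives no rate, so the rate p of symptom-free findings in eyes that otherwise pass is an assumption. The chance of at least one in 10 is 1 − (1 − p)¹⁰:

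| Assumed p | Chance of at least one in 10 |
|---|---|
| 5% | 40% |
| 10% | 65% |
| 20% | 89% |
| 30% | 97% |

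**6. The risk statement beside section VI.** One passage allows only mechanical side effects. The other provides for toxicities, listed separately from non-tolerance of the holder. The brief summary says "Amniotic membrane is considered to be poorly immunogenic", which is a graded statement and not an exclusion. The trial could not confirm the absolute wording: with no non-mechanical event in 10 patients, the two-sided 95% upper limit for the true rate is 1 − 0.025^(1/10) = 30.8%.

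**The case against.** Four stronger readings are tempting, and the documents do not support them.

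- **That the rule passes infected, inflamed or worsening eyes in general.** It does not. Any pain or discomfort fails the fourth point, whatever the cause. Only symptom-free events pass, and the protocol does not say how common these are.
- **That the risk statement and the stopping criteria flatly contradict each other.** The first is a forecast. Section VI is a general contingency list that also covers unforeseen circumstances and calls for a new benefit-risk assessment. The wording is inconsistent and should be reconciled, but it is not a strict contradiction.
- **That the success rule was built on the mechanical-only view.** No text links the two. The rule omits the mechanical effects named in the risk section and includes a symptom that need not be mechanical, which points the other way.
- **That a misclassified eye would be worn longer as a result.** Section III says "Dependent upon compatibility, the postoperative observation period may be extended to 4 weeks", but does not say that this means the four-point rule. *Following visits* ties longer wear to individual assessment.

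It can also be argued that harm is looked for outside the endpoint, through inspections, photographs and the final examination, and that safety may properly be reported beside a device-fit endpoint, with listings left to an analysis plan not shown. This has force for the listings. It does not rescue the endpoint, because the protocol itself fixes the success definition and the primary objective is compatibility, not fit alone.

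A last objection concerns the remedy. Failing an eye for any new finding of any cause would score progression of the underlying disease as device failure and mix the healing question into the primary one. This stands, and the added item has to be limited to findings possibly related to holder or membrane.

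**Conclusion.** The point holds in this form: the success rule has no objective ocular item, so an eye with a device- or membrane-related finding but no pain or discomfort is counted as compatible, and the secondary target does not correct for this. This follows from the text alone. Each such eye adds 10 percentage points to the success proportion. How many there would be cannot be derived; the probabilities shown rest on assumed rates. The protocol sets no success threshold, so the effect is on what the proportion means and not on a pass/fail decision. The change should be made because it alters what the primary result can conclude. The absolute wording of the risk statement is a smaller matter and would not merit a point by itself.

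**What to change.** - Add a fifth point to the success definition: no new or worsened ocular finding that the investigator judges possibly related to the holder or the membrane, including conjunctival dents or pressure marks, inflammation, infection, and corneal worsening against baseline. Assess it at the existing examinations on days 1, 3 and 7, and at the later final visit if wear is extended.
- List all other ocular findings per patient, so that a reader can check the judgements of relatedness.
- Record the secondary outcome as improved, unchanged or worsened.
- Reword the mechanical-only sentence in the risk-benefit assessment so that it agrees with the item "unacceptable risks and toxicities occur" in section VI. How the two are reconciled is for the sponsor and the investigator.

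The cost is protocol wording and a line or two on forms for visits that already take place. There are two downsides. The success proportion may be lower, by 10 points per reclassified patient. Relatedness also rests on investigator judgement in an open study, which the per-patient listing makes visible but does not remove.
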